### Design and participants

2.1

This study protocol was registered in ClinicalTrials.gov (ID: NCT07027397) and approved by the Clinical Research Ethics Committee of the Toledo Hospital Complex (ID: 710P). The present protocol will be conducted in accordance with the SPIRIT (Standard Protocol Items: Recommendations for Interventional Trials) statement (Chan et al., 2013; Supplementary Table S1). Adults aged ≥65 years living in two nursing homes (Toledo, Spain) will participate in this research. Participants will be informed about the characteristics of the study and will provide their signed consent. The study will include a 4-week control period, followed by 9 months of VBRT in the leg press exercise and a 6-month follow-up in which no exercise intervention will be conducted. All participants will be allocated into the intervention group due to ethical reasons (Izquierdo et al., 2025), and thus the control period will serve as the comparator condition. Participants will be randomized in two experimental groups: 10%VL group or 20%VL group. A randomization sequence stratified by theoretical maximal isometric force (F_0_) and sex will be used to assign participants to both groups.

Following our intentionally pragmatic and translational perspective to investigate the effects of VBRT on skeletal muscle size, muscle function, physical performance, disability, cognitive function, and frailty, the exercise intervention will be conducted over a whole season, including periods in which the intervention will be paused (e.g., Christmas, Easter, summer holidays) and then restarted. Thus, the main outcomes will be assessed at six specific time points as detailed in Figure 1: prior to a 4-week control period (Pre-control), at baseline (T0), post 6 weeks (T1), post 12 weeks (T2), post 23 weeks (T3), and post 39 weeks (T4). Upon completion of the VBRT, a final follow-up will be conducted after 6 months of usual care (T5).

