**FIGURE 1 F1:**

Experimental design overview. The study comprises three phases: a 4-week control period, a 9-month velocity-based resistance training (VBRT) intervention and a 6-month follow-up period. Assessment time points are indicated at specific weeks (w): T0 indicates baseline; T1-T4, intervention assessments; and T5, final follow-up.

The required sample size was determined on the basis of muscle function, using the 5-rep sit-to-stand (STS) muscle power test (Alcazar et al., 2018). According to previous research conducting exercise interventions in nursing home residents (Gutiérrez-Reguero et al., 2024), a within-group difference of +0.64 W·kg^−1^ (95%CI: +0.39 to +0.89) in relative muscle power was expected. Using this effect size (ES = 0.91), a required sample size of 15 participants was calculated in the G*Power software, assuming α = 0.05 and power = 90%. Assuming a maximum loss to follow-up of ∼35%, we will recruit 27 nursing home residents aged ≥65 years to address our primary objective. Exclusion criteria will include: i) uncontrolled hypertension, unstable or exercise-induced angina pectoris or myocardial ischemia or any other medical condition incompatible with physical exercise, ii) bedridden or unable to walk with assistance, and iii) terminal illness. The study will be performed in accordance with the Helsinki Declaration.

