### Statistical analysis

2.5

Data will be presented as mean and standard deviation or 95% confidence interval unless otherwise stated. Normality of distribution will be assessed by the Shapiro–Wilk test. To analyze the effect of VBRT on all outcomes in the whole sample (primary objective), linear mixed-effect models (LMM) will be fitted using Restricted Maximum Likelihood (REML) estimation. The model will include time as a fixed effect and participant ID as a random effect. The control period will be included in the LMM as an additional time level. This will allow for the comparison of change during the non-exercise period against the time-adjusted changes observed during the VBRT intervention. For the secondary analysis, between-group differences after the VBRT (secondary objective I) will be assessed using the same LMM framework and including time and group (10% vs. 20 VL) as fixed effects, and participant ID as a random effect. The residual effects derived from the VBRT program after 6 months of follow-up will be analyzed similarly, with time as a fixed effect and participant ID as a random effect. To preserve Intention-to-Treat (ITT) principles, training adherence will not be included in the primary model. A secondary per-protocol sensitivity analysis using LMM with REML estimation will be conducted across all objectives, including only participants who completed ≥80% of the exercise sessions. Pairwise comparisons will be adjusted using the Bonferroni method. Cohen’s *d* effect sizes will be calculated using the pooled baseline standard deviation and interpreted as: trivial (<0.20), small (0.20–0.49), moderate (0.50–0.79), and large (>0.80). Statistical analyses will be conducted using SPSS (version 26.0, SPSS Inc., United States), and the level of significance will be set at α = 0.05.

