
Regarding the comparison of different VL thresholds in our VBRT program (secondary objective), both intra-set fatigues (i.e., 10% and 20%VL) have been proven effective in improving physical performance and muscle strength in older adults from residential care facilities or day centers (Marques et al., 2024). This is the only study to compare different VL exclusively among institutionalized older adults. In line with the expected findings, we anticipate no significant differences between the 10%VL and 20%VL groups in physical and muscle function, frailty and disability over the experimental period. Given that this between-group comparison is a secondary objective and the study is not formally powered to detect differences between VL thresholds, this analysis should be interpreted as exploratory and hypothesis-generating, with the resulting effect sizes serving to inform sample size calculations for future adequately powered trials. Although higher VL thresholds (i.e., 40%VL) are associated with greater hypertrophy in young populations (Pareja-Blanco et al., 2020), lower VL thresholds (i.e., 10–20%VL) may generate less fatigue and be sufficient to elicit structural adaptations in older adults living in nursing homes, characterized by low muscle mass (Kimyagarov et al., 2012), with comparable results between groups. If these hypotheses are confirmed, VBRT with 10% VL would be an effective and efficient approach for improving health parameters while imposing lower fatigue (Marques et al., 2022).

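### The 10% vs 20% VL model does not adjust for the two pre-training measurements of the main outcomes, so the randomised comparison is less precise than the data allow and sensitive to chance baseline imbalance

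*Protocol article*

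**What the plan says.** Section 2.1 (Design and participants) states that "the main outcomes will be assessed at six specific time points as detailed in Figure 1". The first two of these precede any training: "prior to a 4-week control period (Pre-control), at baseline (T0), post 6 weeks (T1", and so on through T4, with T5 as the later follow-up. Randomisation is stratified by F0 and sex.

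Section 2.5 (Statistical analysis) describes the whole-sample model and says how the pre-training period enters it: "The control period will be included in the LMM as an additional time level". The comparison of VL thresholds uses the same framework, "including time and group (10% vs. 20 VL) as fixed effects, and participant ID as a random effect". The section names no baseline covariate, no constraint of equal group means before training and no group-by-time term.

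The Discussion says that "the study is not formally powered to detect differences between VL thresholds" and calls the analysis exploratory, "with the resulting effect sizes serving to inform sample size calculations for future adequately powered trials".

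**The concern.** The 10% vs 20% VL contrast is the only randomised comparison in the trial. In the stated model the group term is free at the pre-training visits as well as after them, so the participant random effect does not act as a baseline adjustment. It describes correlation within a person, but it does not use the fact that the arms had the same expected value before training. With 27 participants, chance differences in starting level can be of the same order as a small or moderate effect on the protocol's own Cohen's d scale.

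Two things are at stake. One is the width of the interval around the group difference. The other is how far a single realised estimate reflects where the arms happened to start. Both matter because the effect sizes are to be handed on to the planning of later trials.

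**Working it through.** **Inputs from the document.** Recruited N is 27 and loss to follow-up about 35% (section 2.1), so 27 × 0.65 = 17.55, or about 17 remaining. There are two pre-training visits and four visits T1-T4 (section 2.1). The model is that of section 2.5. The document gives no figure for the between-group comparison, so there is none to reproduce.

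**Assumptions.** Allocation is 1:1 (14 vs 13, later 9 vs 8). Outcomes have unit SD. The correlation ρ is equal between all visits; no value is given, so 0.5, 0.7 and 0.8 are shown. Stratification is ignored.

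**Step 1: size of chance imbalance.** The SD of the baseline difference at one visit is √(1/n₁ + 1/n₂).
- 14 vs 13: √(1/14 + 1/13) = 0.39 SD (95% range ±0.75). The chance of exceeding 0.2 SD is 60%, and of exceeding 0.5 SD 19%.
- 9 vs 8: √(1/9 + 1/8) = 0.49 SD (±0.95).

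These are upper-end figures for F0 and outcomes closely tied to it, because the allocation is stratified by F0 and sex.

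**Step 2: variance of the T4 group difference**, in units of SD²(1/n₁ + 1/n₂).
- Unadjusted level: 1
- Change from T0: 2(1 − ρ)
- Change from the mean of Pre-control and T0: 1 + (1 + ρ)/2 − 2ρ = 1.5(1 − ρ)
- Adjusted for that mean: 1 − ρ²/[(1 + ρ)/2] = 1 − 2ρ²/(1 + ρ)

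| ρ | Level | Change from T0 | Change from mean | Adjusted |
|---|---|---|---|---|
| 0.5 | 1 | 1.00 | 0.75 | 0.667 |
| 0.7 | 1 | 0.60 | 0.45 | 0.424 |
| 0.8 | 1 | 0.40 | 0.30 | 0.289 |

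Variance cut from adjustment, for example 1 − 0.424/0.45 = 6%:

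| ρ | vs level | vs change from T0 | vs change from mean |
|---|---|---|---|
| 0.5 | 33% | 33% | 11% |
| 0.7 | 58% | 29% | 6% |
| 0.8 | 71% | 28% | 4% |

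At 14 vs 13 the standard error of the unadjusted level is 0.385 SD. Adjusted, it is 0.314 (ρ = 0.5), 0.251 (0.7) or 0.207 (0.8).

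**Step 3: what this means for power.** The true difference of 0.8 SD is purely illustrative. The test is two-sided at 0.05 by the noncentral t. The adjusted column is charged one degree of freedom and a small-sample inflation for the covariate.

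| N, ρ | Level | Change from T0 | Change from mean | Adjusted |
|---|---|---|---|---|
| 27, 0.5 | 51% | 51% | 63.5% | 66.6% |
| 27, 0.8 | 51% | 88% | 95.4% | 95.2% |
| 17, 0.5 | 34% | 34% | 42.8% | 44.0% |
| 17, 0.8 | 34% | 68% | 80.2% | 78.4% |

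**Step 4: do the two remedies agree?** 300 simulated REML fits used 13 vs 14 participants, ρ = 0.7 and a true difference of 0.50 SD at T1-T4. The covariate model and the equal-baseline model both recovered a mean of 0.50 with an SD of 0.16. Their correlations with the pre-training imbalance were 0.05 and 0.01.

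**The case against.** **Is this only the missing group-by-time term under another name?** In part. A reader might infer from the stated model that most of the starting difference passes into the result. For the group coefficient without group-by-time, 78% (ρ = 0.5) to 93% (ρ = 0.8) of it does. That figure is a consequence of having no interaction and should not be counted as a separate harm here.

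**With an interaction, is anything left?** Less. Both pre-training visits are already in the model as responses, so a change from their mean could be taken without any covariate. Against that contrast the variance cut is 11% or less. The power gain is about 3 points at most, and power is slightly lower at ρ = 0.8 once the degree of freedom is charged. A reader might therefore infer a sizeable power gain whatever the comparator, and the figures do not support that. The objection stands as a limit on size. But section 2.5 specifies neither that contrast nor the interaction.

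**Is it bias?** A reader might infer so. Under randomisation chance imbalance averages to zero, and a valid interval for the unadjusted difference already allows for it. What remains is lost precision and an estimate that depends on the imbalance actually realised.

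**Does stratification deal with it?** Partly. F0 and sex plausibly protect F0 and related strength or power outcomes. They do much less for MMSE, Barthel or Lawton.

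**It is exploratory, and no difference is expected.** True, and this limits the consequence. The hand-over of effect sizes to later trials is still a reason to estimate them as well as the data allow.

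**Could this be left to a fuller document?** Detail could. But the article states this model's terms explicitly, so the point concerns what is stated.

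**Conclusion.** The point holds as one of efficiency and of sensitivity to realised imbalance. The stated model for secondary objective I uses the two pre-training measurements of the main outcomes only as response rows, and so gives up information that has already been collected. The variance given up at T4 is 33-71% relative to an unadjusted level, 28-33% relative to change from T0, and only about 4-11% relative to change from the mean of both visits. All of these rest on an assumed equal correlation of 0.5 to 0.8 and on 1:1 allocation. The effect is likely to be greatest for outcomes not closely tied to F0 and sex.

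The document supports the point for the main outcomes; it does not say that every outcome is measured at both visits. The whole-sample primary analysis is not touched, and the group comparison remains exploratory whichever model is used.

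**What to change.** Amend the sentence on secondary objective I in section 2.5 in one of two ways:
- Take T1-T4 as responses, with group, time, group-by-time and the participant's own pre-training value of that outcome (mean of Pre-control and T0) as fixed effects, and participant as a random effect.
- Keep all visits as responses and constrain the two groups to a common mean at Pre-control and at T0.

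Report the adjusted group difference at T4 with its 95% confidence interval, and base the effect size offered to future trials on it. Settle the choice before outcomes are compared by group, so that adjustment is not decided after the imbalance is known.

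The cost is a change of wording, one covariate in the SPSS model and about one degree of freedom. It needs no additional visits or participants.

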## Discussion

3

This protocol is designed to evaluate the effects of a VBRT program on skeletal muscle size, muscle function, physical performance, disability, cognitive function, and frailty in nursing home residents using a pragmatic and translational approach. In addition, it will compare the effects derived from the use of two different VL thresholds (10% vs. 20% VL), and will examine the residual effects of VBRT after 6 months of exercise cessation.

There are several potential advantages for using a VBRT approach. First, VBRT represents a valid, and most importantly, feasible method to objectively monitor and prescribe RT parameters (Weakley et al., 2021; González-Badillo et al., 2022). This might be especially important for vulnerable frail populations (such as institutionalized older people) to better adjust the RT dose on an exercise session basis. In addition, VBRT relies on performing each repetition as fast as possible, maximizing adaptations in muscle function (Pareja-Blanco et al., 2014), especially for rapid force production and muscle power. Of note, the ability to apply force rapidly (i.e., rate of force development, RFD) and the rate of producing mechanical work (i.e., muscle power) decreases abruptly with aging (Thompson et al., 2014; Alcazar et al., 2021a), and therefore, their optimization is crucial for maintaining mobility and fall prevention at older age (Hester et al., 2021).

Based on the previous evidence on RT intervention in general and frail older populations, we theorize that VBRT will provoke positive adaptations in the investigated outcomes throughout the course of the study in our institutionalized older adults. Nevertheless, different time courses for the different exercise-induced adaptations might be observed throughout the proposed intervention. Short-term benefits (i.e., post 6 weeks) in frailty, muscle function and physical performance are expected among institutionalized or pre-frail older adults (Serra-Rexach et al., 2011; Courel-Ibáñez et al., 2022; Marques et al., 2022; Buendía-Romero et al., 2023; Baltasar-Fernandez et al., 2024). Our research group has previously demonstrated that 6 weeks of RT on the leg press exercise is an effective stimulus to promote muscle function adaptations and improve frailty in community-dwelling frail older adults (Baltasar-Fernandez et al., 2024). In contrast, in line with previous studies, we do not anticipate significant short-term changes in cognitive function (Coelho-junior et al., 2020), disability (Baltasar-Fernandez et al., 2024) or skeletal muscle size (Lixandrão et al., 2016). Additional benefits are expected in physical and muscle function when a longer period of RT is applied. Studies analyzing the time course of physical function and strength adaptations in institutionalized older adults show accumulated improvements (+7%–24%) after extended 10 weeks of exercise training (Courel-Ibáñez et al., 2022). Moreover, longer periods of RT (as proposed in the current study protocol) could lead to significant enhancements in muscle size, disability and cognitive function. Previous research in institutionalized older adults conducting resistance training for 12 weeks has reported improvements in quadriceps femoris ACSA even in nonagenarians (Cadore et al., 2014a). This requirement for a longer duration would be consistent with previous studies analyzing the time-course of muscle mass adaptation in older adults, where changes in vastus lateralis ACSA were observed only after 9 weeks of resistance training (Lixandrão et al., 2016). Regarding cognitive function and disability, previous studies in nursing home residents have reported improvements in MMSE score and Barthel Index after 12 weeks of exercise training (Cancela Carral et al., 2017; Gutiérrez-Reguero et al., 2024). Indeed, previous systematic reviews propose that interventions lasting longer than 16 weeks are required to maximize the effects of RT as an important moderator of cognitive improvements in older adults (Coelho-junior et al., 2020). Therefore, the duration of this protocol with a 9-month intervention period could be crucial to obtaining meaningful hypertrophy and cognitive benefits, as well as noteworthy disability reductions.

Regarding the comparison of different VL thresholds in our VBRT program (secondary objective), both intra-set fatigues (i.e., 10% and 20%VL) have been proven effective in improving physical performance and muscle strength in older adults from residential care facilities or day centers (Marques et al., 2024). This is the only study to compare different VL exclusively among institutionalized older adults. In line with the expected findings, we anticipate no significant differences between the 10%VL and 20%VL groups in physical and muscle function, frailty and disability over the experimental period. Given that this between-group comparison is a secondary objective and the study is not formally powered to detect differences between VL thresholds, this analysis should be interpreted as exploratory and hypothesis-generating, with the resulting effect sizes serving to inform sample size calculations for future adequately powered trials. Although higher VL thresholds (i.e., 40%VL) are associated with greater hypertrophy in young populations (Pareja-Blanco et al., 2020), lower VL thresholds (i.e., 10–20%VL) may generate less fatigue and be sufficient to elicit structural adaptations in older adults living in nursing homes, characterized by low muscle mass (Kimyagarov et al., 2012), with comparable results between groups. If these hypotheses are confirmed, VBRT with 10% VL would be an effective and efficient approach for improving health parameters while imposing lower fatigue (Marques et al., 2022).

In terms of the residual benefits persisting 6 months after exercise cessation (secondary objective), a recent meta-analysis confirms the residual effects of exercise on physical performance in older adults (Buendía-Romero et al., 2025), however, the evidence with institutionalized older adults is scarce, and the residual effect of VBRT remains unexplored. We hypothesize that a deconditioning will occur in skeletal muscle size, muscle function, physical performance, disability, cognitive function, and frailty after 6 months of usual care without regular exercise in older adults, as supported by previous studies in non-institutionalized older adults (Hakkinen et al., 2000; Zech et al., 2012; Coetsee and Terblanche, 2015; Grgic, 2022). However, despite the predictable decline in several outcomes from the levels achieved immediately after the VBRT intervention, these may remain significantly elevated compared to baseline after several months of exercise cessation (Baltasar-Fernandez et al., 2024). Notably, a rapid decline is common in institutionalized older adults (Serra-Rexach et al., 2011; Telenius et al., 2015; Caldo-Silva et al., 2021), so the long-lasting benefits could be conditioned by the individual exercise response and the age of the participants recruited in this study (Toraman, 2005; Buendía-Romero et al., 2025). Despite the advanced age of institutionalized older adults, the large benefits expected from the VBRT intervention are expected that contribute to significant residual effects after 6 months of usual care. This follow-up is crucial for understanding whether VBRT can induce benefits not only during a prolonged training period but also residual effects.

Due to the pragmatic and translational nature of this study, its results will be highly relevant for both nursing home staff and residents. If the long-term adherence and benefits derived from VBRT are proven in institutionalized older adults, device-based approaches in RT could be a strategy to optimize exercise-related health benefits. Additionally, the findings would support the implementation of innovative actions to promote exercise practice in people living in nursing homes.

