**Discussion:**

We hypothesize that VBRT will exhibit meaningful benefits in muscle size, muscle function, physical performance, disability, cognitive function and frailty among institutionalized older adults, with no significant differences between 10% and 20% VL thresholds. While deconditioning is predictable after 6 months of exercise cessation, the investigated outcomes are expected to remain significantly and positively elevated compared to baseline values. This study will help to identify innovative actions to improve overall health and endorse exercise practice in older adults living in nursing homes.

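### The velocity-loss hypothesis is worded so that a non-significant result confirms it, in a comparison the article itself calls unpowered

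*Protocol article*

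**What the plan says.** The Introduction makes the comparison of 10% and 20% VL secondary objective I. The Discussion paragraph of the Abstract gives the hypothesis as benefit from training "with no significant differences between 10% and 20% VL thresholds". Section 3 (Discussion) repeats it: "we anticipate no significant differences between the 10%VL and 20%VL groups in physical and muscle function, frailty and disability over the experimental period".

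Section 3 then limits the comparison. It states that "the study is not formally powered to detect differences between VL thresholds" and that "this analysis should be interpreted as exploratory and hypothesis-generating", with the effect sizes to be used for sizing later trials. Two sentences further on comes the inference at issue: "If these hypotheses are confirmed, VBRT with 10% VL would be an effective and efficient approach for improving health parameters while imposing lower fatigue".

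Section 2.5 plans a linear mixed model with time and group as fixed effects, Bonferroni-adjusted pairwise comparisons and a 0.05 significance level. It also plans Cohen's d and allows for 95% confidence intervals. The article links no margin to the no-difference hypothesis.

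The sample size in Section 2.1 serves the whole-sample, within-group objective only: "a within-group difference of +0.64 W·kg^−1^ (95%CI: +0.39 to +0.89) in relative muscle power was expected", and "Using this effect size (ES = 0.91), a required sample size of 15 participants was calculated in the G*Power software".

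**The concern.** A hypothesis phrased as absence of statistical significance is met whenever p exceeds 0.05. That happens when the groups really are alike, and also when the sample is too small to separate them. The caveat in Section 3 accepts that the sample is too small for this comparison, yet the later sentence treats the hypothesis as something the same data could confirm and attaches a practical statement about 10% VL to it. The two statements pull against each other.

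At stake is what the trial may say on secondary objective I. Read literally, the text lets a null result from an imprecise comparison stand as support for comparability, and this becomes more likely as dropout rises.

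**Working it through.** **1. The plan's own figure.** Paired t-test, effect size 0.91, two-sided α = 0.05, power 90%. With n = 15 the noncentrality is 0.91 × √15 = 3.52, the critical t on 14 df is 2.145, and power is 0.906. With n = 14 power is 0.882. The stated 15 is reproduced, but it concerns change over time in the whole sample and says nothing about the contrast between groups.

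**2. Numbers per group.** 27 recruited gives 13 and 14, assuming 1:1 allocation (the article states no ratio). After 35% loss, 27 × 0.65 = 17.55, or about 9 and 9.

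**3. Standard error of the between-group difference, in SD units.**
- T4-only comparison: SE = √(1/n₁ + 1/n₂).
- Change from T0 to T4: SE = √(1/n₁ + 1/n₂) × √(2(1 − ρ)), where ρ is the correlation between T0 and T4. The article gives no ρ, so 0.7–0.9 is assumed.

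Example, 13/14: √(1/13 + 1/14) = 0.385. At ρ = 0.8 the factor is √0.4 = 0.632, so SE = 0.244. For 9/9 the values are 0.471 and 0.298.

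**4. Chance of p > 0.05 when the true difference is 0.5 SD** (the article's lower bound for a moderate effect). Two-sample t-test, noncentrality 0.5/SE, two-sided 0.05, df = n₁ + n₂ − 2. The last column is the critical t (2.060 on 25 df, 2.120 on 16 df) × SE.

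| Contrast | Groups | SE | P(non-significant) | 95% CI half-width |
|---|---|---|---|---|
| T4 only | 13/14 | 0.385 | 76% | 0.79 |
| T4 only | 9/9 | 0.471 | 83% | 1.00 |
| Change, ρ = 0.7 | 13/14 | 0.298 | 64% | 0.61 |
| Change, ρ = 0.7 | 9/9 | 0.365 | 75% | 0.77 |
| Change, ρ = 0.8 | 13/14 | 0.244 | 49% | 0.50 |
| Change, ρ = 0.8 | 9/9 | 0.298 | 65% | 0.63 |
| Change, ρ = 0.9 | 13/14 | 0.172 | 20% | 0.36 |
| Change, ρ = 0.9 | 9/9 | 0.211 | 39% | 0.45 |

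In every setting dropout from 13/14 to 9/9 raises the chance of non-significance. For T4 only, the difference detectable with 80% power is 1.12 SD (13/14) or 1.41 SD (9/9).

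**5. Could comparability be shown with a margin?** For illustration take 0.5 SD, a true difference of zero, and two one-sided tests at 5% (90% CI inside ±0.5 SD) on the change contrast. Power is about 28% at 13/14 and 8% at 9/9 for ρ = 0.8, and 76% and 47% for ρ = 0.9. At ρ = 0.8 the expected 90% half-widths are 1.708 × 0.244 = 0.42 (13/14) and 1.746 × 0.298 = 0.52 (9/9).

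Bonferroni adjustment would raise the chance of non-significance. Using the intermediate visits in the mixed model could lower it somewhat. Neither is included above.

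**The case against.** The strongest reply is that the article has already dealt with this. Section 3 tells the reader to treat the comparison as exploratory and names effect sizes as its product. Section 2.5 plans Cohen's d and allows for confidence intervals, so much of an estimation approach is in place. No sentence says outright that p > 0.05 equals confirmation. The hypotheses referred to are plural, and the claim that low thresholds suffice can be examined through within-group change. All of this stands, and it lowers the severity. It does not settle the matter: the caveat never says that a null result is inconclusive, the Abstract carries the hypothesis without the caveat, and the part about comparable groups can rest only on the between-group contrast.

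Three stronger readings are tempting and are not supported:
- *That the plan will recommend 10% VL or declare it superior to 20% VL.* The sentence is conditional and calls 10% VL effective and efficient with lower fatigue. It makes no claim of superiority.
- *That the no-difference result is all but built in.* The chance of non-significance at 0.5 SD falls to 20% at 13/14 with ρ = 0.9. Figures of 91–93% for a group effect averaged over visits need an assumed gradual build-up of the difference. With the full difference present from T1 they are 84–89%. The article supports neither pattern over the other.
- *That equivalence within 0.5 SD could never be shown.* The expected 90% half-width exceeds 0.5 SD at 9/9 with ρ of 0.8 or below and at 13/14 with ρ = 0.7, but not in the more favourable settings.

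The lack of an equivalence test is not itself a fault in a condensed article with an exploratory objective.

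**Conclusion.** The concern holds as a minor inconsistency of wording. The hypothesis of no significant difference, together with the conditional conclusion about 10% VL, conflicts with the article's own statement that the comparison is unpowered and hypothesis-generating. At a true difference of 0.5 SD, non-significance would occur in roughly half to five-sixths of trials under the central assumptions (49–65% for change at ρ = 0.8, 76–83% for T4 only). Over ρ = 0.7–0.9 the range for change is 20–75%. These figures rest on 1:1 allocation, 35% loss, simple t-test contrasts, and a correlation and true difference chosen for illustration. The logical point needs none of them: non-significance in an imprecise comparison is not evidence of comparability.

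**What to change.** Three changes of wording:
1. In the Abstract and Section 3, restate the expectation for secondary objective I as estimation of the between-group difference in T0–T4 change, reported with its 95% CI.
2. Add to the exploratory caveat that a non-significant result is inconclusive about comparability of the two thresholds.
3. Remove the sentence that begins with confirmation of the hypotheses, or reword it so that any statement about 10% VL rests on within-group change only.

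If the sponsor wants to be able to claim comparability, a margin must be justified and fixed before the data are seen, and the claim made only if the confidence interval lies wholly inside it. The 0.5 SD used above is an illustration and has no basis in the article.

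The cost is a few sentences and the loss of a comparability conclusion that the design is unlikely to support. Recruitment, conduct, the primary objective and the planned model do not change.
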